## **METHODOLOGY**

**Setting.** The study will be carried out in the ASSIR units of Mollet del Vallés, Granollers, Badalona in the province of Barcelona, “Metropolitan Nord” Area and the ASSIR Eixample Dret, “Barcelona City” Area, in Primary Care of the Catalan Institute of Health. In these units, a total of 6,496 first pregnancy visits were made in the year 2015.

The study will last for two years.

**Design.** An experimental, multicentre, randomized cluster trial and parallel study will be carried out that will allow to know the effectiveness of a counselling intervention of the birth plan based on “shared decision making”.

## **Subjects**

Target population Pregnant women with prenatal care in the health care centres of the ASSIR from Catalonia

Inclusion criteria. Older pregnant women with prenatal care in the centres study, with childbirth in the reference hospitals, who wish to participate in the study and want to fill in the birth plan

Exclusion criteria. Illiteracy, language barrier, drug addiction, alcoholism, grade 2, 3 and 4 heart disease, severe associated maternal pathology, type I-II diabetes, uterine malformation, diagnosed foetal malformation, threatened preterm birth, twin or multiple pregnancy, cervical incompetence, previous perinatal death, intrauterine growth retardation, placenta previa, isoimmunization, mild-severe preeclampsia, premature rupture of membranes, maternal infection.

Sample size. The sample calculation has been made based on the main variable of the study “presentation of birth plans”. Based on the descriptive pilot study (n = 211 pregnant women), 48% of the women who receive the usual advice presented the

birth plan to the hospital. It is estimated that this prevalence may be higher in women who receive counselling, around 68%. In this study, a randomized, multicentre and parallel experimental design in clusters is proposed (4 ASSIRs participate). Applying an alpha error of 5%, a beta error of 20% and taking into account the influence of the clusters in the analysis, a total of 133 are required in the control group and 133 in the intervention group. 15% loss to follow-up has been estimated. The calculation has been carried out using the macros of SPSS V22. An interim analysis will be performed to assess whether the sample size needs to be recalculated so that there is sufficient power for the subgroup analysis.

Sampling technique. In the random assignment of ASSIR, the characteristics of the reference hospitals will be taken into account, since they have different levels of care. Thus, two ASSIRs will be assigned to the intervention group and two to the control. For this assignment, the Epidat 4.1 program will be used. This type of assignment has been chosen to avoid contamination among midwives who will or will not receive specific training on birth plan counselling based on shared decision making.

The sampling technique of pregnant women within each ASSIR will be consecutive and proportional to the number of first visits (see table 1).

Table 1. Proportional sampling according to the number of first ASSIR visits

| ASSIR             | First visits | Proportion | Sample size |
|-------------------|--------------|------------|-------------|
| Mollet del Vallés | 1017         | 15.1%      | 41          |
| Badalona          | 1933         | 29.6%      | 79          |
| Granollers        | 2260         | 35.7%      | 94          |
| Dreta Eixample    | 1286         | 19.6%      | 52          |
| Total             | 6496         | 100%       | 266         |

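### The stated 80% power for 48% v 68% depends on an unstated ICC and a normal critical value; a test that estimates between-cluster variance from two ASSIRs per arm has about 36%

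*Protocol*

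**What the plan says.** The sample-size paragraph of the Protocol (Methodology, Subjects) sets out the basis: "The sample calculation has been made based on the main variable of the study “presentation of birth plans". From a pilot study, "48% of the women who receive the usual advice presented the" birth plan to the hospital. For the intervention arm, "It is estimated that this prevalence may be higher in women who receive counselling, around 68" per cent. The error rates are given as "Applying an alpha error of 5%, a beta error of 20" per cent. The result is stated as "taking into account the influence of the clusters in the analysis, a total of 133 are required in the control group", with 133 also in the intervention group. The next sentence reads "15% loss to follow-up has been estimated", without saying whether the 133 already contains that loss.

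The same paragraph describes the design: a "parallel experimental design in clusters is proposed (4 ASSIRs participate"). The sampling paragraph adds "Thus, two ASSIRs will be assigned to the intervention group and two to the control", and says that the characteristics of the reference hospitals will be considered in the assignment because their levels of care differ. It does not say whether this means pairing. Table 1 gives cluster sizes of 41, 79, 94 and 52.

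No ICC, design effect or degrees of freedom appears. The Analysis section names chi-square and Student's t tests and an unspecified multivariate analysis.

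**The concern.** The protocol says that it allowed for clustering and then claims a conventional 80% power. An allowance for clustering has two parts. One is inflating the number of women by a design effect. The other is accepting that the treatment effect is judged against variation between clusters, of which there are only four. Inflating the number of women deals with the first part and leaves the second untouched.

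The consequence concerns the main variable. If the analysis respects the clusters, a non-significant result is the more likely outcome even when the full 20-point effect exists, and the stated beta invites readers to take it as an adequately powered negative. If the analysis ignores the clusters, power looks ample but the 5% alpha is not held. An unseen SAP could choose the method of analysis, but it cannot supply degrees of freedom that the design lacks, so this is a matter for the protocol.

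**Working it through.** **Inputs.** From Subjects: p1 = 0.48, p2 = 0.68, difference 0.20, alpha 5% (sidedness not stated; two-sided assumed), power 80%, 133 per arm, 15% loss, two ASSIRs per arm. From Table 1: cluster sizes 41, 79, 94 and 52.

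**Step 1. Individual randomisation.**
n = [1.96·√(2·0.58·0.42) + 0.8416·√(0.48·0.52 + 0.68·0.32)]² / 0.20² = 94.4, so 95 per arm. Other standard formulas give 92 (unpooled), 94 (arcsine) and 105 (continuity-corrected). Inflating 95 or 105 for 15% loss gives 112 or 124, so loss alone does not reach 133.

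**Step 2. Recover the protocol's 133.**
- If 133 includes the loss: 133 × 0.85 = 113 analysed, about 56.5 per ASSIR. Design effect (DE) = 113/94.4 = 1.20. ICC = (1.197 − 1)/55.5 = 0.0036.
- If 133 excludes the loss: DE = 133/94.4 = 1.41, with 66.5 per ASSIR. ICC = 0.409/65.5 = 0.006.

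So 133 is attainable with a small, undisclosed ICC.

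**Step 3. Power as the protocol appears to have computed it.**
SE = √{[0.48·0.52 + 0.68·0.32]·DE/n} = √(0.4672 × 1.20/113) = 0.0704. Then 0.20/0.0704 = 2.84, and with a critical value of 1.96 power is 81%. The stated 80% is reproduced, but only with the normal critical value.

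**Step 4. The same SE with the cluster-level degrees of freedom.**
Four clusters in two arms leave 4 − 2 = 2 df, and t(0.975; 2) = 4.303. Power comes from the noncentral t with noncentrality 0.20/SE and DE = 1 + (m − 1)·ICC, where m is the number analysed per ASSIR.

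| Analysed per arm | ICC | DE | Power, 2 df | Power with 1.96 |
|---|---|---|---|---|
| 113 | 0 | 1.00 | 41% | 87.5% |
| 113 | 0.0036 | 1.20 | 36% | 81% |
| 113 | 0.01 | 1.56 | 30% | 70% |
| 113 | 0.02 | 2.11 | 24% | 57% |
| 113 | 0.05 | 3.78 | 16% | 36% |
| 133 | 0 | 1.00 | 46% | 92% |
| 133 | 0.006 | 1.41 | 36% | 81% |

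Both readings of the loss give about 36%. The choice of sample-size formula matters little: taking DE from 1.08 to 1.23 at 113 per arm moves the 2-df power only between 39% and 35%. The 95% CI half-width at DE 1.20 is 4.303 × 0.0704 = 0.30, or 30 points against a target of 20.

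**Step 5. Unequal clusters.** Simulation with the Table 1 sizes gives 38–39% (after 15% loss) and 43–44% (no loss) at ICC 0, and about 35% and 38–39% at ICC 0.003. The equal-cluster figures are therefore not pessimistic.

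**Step 6. If allocation is paired by hospital level.** One df remains. Power is 19% (113 per arm) to 21% (133 per arm) at ICC 0, and about 18% at the back-solved design effects.

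**Step 7. If clusters are ignored in the test.** The actual alpha is about 7% at ICC 0.003, 12–13% at 0.01 and 31–34% at 0.05.

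**The case against.** **The number 133 is not a miscalculation.** This stands. It follows from a design effect near 1.2 and 15% loss: 95 × 1.19/0.85 = 133. What is at fault is the power attached to it and the missing ICC.

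**Other tests have more power.** A reader might infer that 80% is out of reach at any ICC. The documents do not support that. At ICC exactly 0 an individual-level test is valid and has about 87% to 92% power, and a test corrected with an ICC known from outside the trial would not be limited to 2 df. But the protocol names no such ICC. It says that clusters were taken into account, so it does not assume zero. It also says that the hospitals differ in level of care (Subjects) and that birth plans are agreed with each hospital (Data collection and tools), which makes a zero ICC for this outcome hard to presume.

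**More women could be added.** A reader might infer that more women in the same four ASSIRs would hardly help. That depends on the ICC. At 0.0036 the 2-df power rises to 55% at 266 analysed per arm and 79% at 1,000. At 0.01 its limit is about 59% however many are added. The planned interim recalculation does not settle this, because it is tied to power for the subgroup analysis.

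**The 36% rests on a back-solved ICC and unpaired allocation.** This also stands, so the figure has to be given with those conditions.

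**Conclusion.** The concern holds in a conditional form. The protocol's 80% is obtained only with an unstated ICC of about 0.0036 to 0.006 and a large-sample critical value. For an analysis that estimates between-cluster variance from these four ASSIRs, power for 48% v 68% is about 36% whether or not 133 includes the loss. It is at most about 41% (113 analysed) to 46% (133 analysed) for that kind of test, and no more than about 21% if allocation is paired. This assumes a two-sided 5% test and roughly equal clusters; the Table 1 sizes make little difference.

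The documents do not show that the trial will be inconclusive. That depends on the analysis used: a plain chi-square test would instead bring an inflated false-positive rate.

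**What to change.** Keep 266 women and rewrite the sample-size paragraph:

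- State the ICC assumed, its source, and the design effect.
- State whether 133 per arm includes the 15% loss.
- State whether the ASSIRs are paired by hospital level before assignment.
- Replace the unqualified 20% beta with the small-df power that follows. If allocation is unpaired this is about 36%, with the range over ICC (41% at 0, 30% at 0.01 and 16% at 0.05 with 113 analysed per arm). If it is paired, give the 1-df figure.
- Say that the primary effect will be reported as an estimate with a CI on the cluster-level df (t with 2 df if unpaired), and that a non-significant result is not evidence of no effect.

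The cost is rewording, with no extra women. The downside is that the stated power becomes much less favourable, and rewording does not raise it. Should the sponsor want 80% under a cluster-level test, the number of ASSIRs is the main lever: at about 56 analysed women each, roughly 4 per arm at ICC 0.003–0.01 and 8 per arm at ICC 0.05.

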## **Objectives**

To evaluate the effectiveness of a counselling intervention in the birth plan, based on “shared decision-making”, in pregnant women in relation to the presentation of the birth plan to the hospital and on preferences regarding aspects related to childbirth and satisfaction with the childbirth, compared to the standard counselling.

To evaluate the effectiveness of a counselling intervention in the birth plan, based on “shared decision-making”, in pregnant women in relation to the degree of information received in the pregnancy about the childbirth, with respect to the standard counselling

**Design.** A cluster randomised trial study, multicentre, parallel which will reveal the effectiveness of counselling intervention birth plan will be held based on "shared decision-making".

**Participants:** Pregnant women with prenatal care in Sexual and Reproductive Health Care (ASSIR) centres and who wish to participate in the study. Sample size: 266 pregnant women will be studied, 133 in each of the groups.

**Statistical analysis:** Descriptive analysis will be performed in all the variables and a bivariant analysis through hypothesis testing. Confidence interval CI will be settled on 95%. A multivariate analysis, relative risks with a CI of 95%.

**Keywords:** birth plan, assessment, midwives, satisfaction, shared decision making.

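### Table 1 fixes the ASSIR quotas before the two-against-two allocation, so the arms would be 135/131, 120/146 or 93/173 rather than the stated 133 each, and its Proportion column is miscalculated

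*Protocol*

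**What the plan says.** The Abstract (Participants) states the target: "266 pregnant women will be studied, 133 in each of the groups". The Sample size paragraph under Subjects repeats it: "a total of 133 are required in the control group and 133 in the intervention group".

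The Sampling technique paragraph sets the allocation: "two ASSIRs will be assigned to the intervention group and two to the control". It restricts the randomisation only in general terms: "In the random assignment of ASSIR, the characteristics of the reference hospitals will be taken into account". It does not mention ASSIR size.

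The same paragraph then sets the recruitment rule: "The sampling technique of pregnant women within each ASSIR will be consecutive and proportional to the number of first visits". Table 1 turns this into one quota per ASSIR, giving first visits, proportion and sample size. Two of its rows read "Mollet del Vallés | 1017 | 15.1% | 41" and "Granollers | 2260 | 35.7% | 94". The other quotas are 79 for Badalona and 52 for Dreta Eixample. The totals are 6496 visits, 100% and 266 women.

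**The concern.** Table 1 shares 266 women across all four ASSIRs in one step, without regard to which two will form an arm. The 133-per-arm target applies to arms that exist only after randomisation. Both instructions can be met only if the drawn pair of quotas happens to add to 133. If it does not, sites have two incompatible targets: the table, or the arm size behind the sample size calculation. At stake are the balance between arms and, in one pairing, some efficiency.

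Separately, the Proportion column should be each ASSIR's visits divided by 6496, and the quotas should follow from it. If they do not, the table does not implement the rule it is meant to illustrate.

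**Working it through.** **Inputs (Protocol, Subjects and Table 1).** First visits: Mollet 1017, Badalona 1933, Granollers 2260, Dreta Eixample 1286. Quotas: 41, 79, 94, 52. Target: 133 per arm. Presentation rates: 48% and 68%. Alpha 5% (taken as two-sided; sidedness is not stated), beta 20%, loss 15%.

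**1. Totals.** 1017 + 1933 + 2260 + 1286 = 6496, which agrees with the Setting paragraph. 41 + 79 + 94 + 52 = 266. 15.1 + 29.6 + 35.7 + 19.6 = 100.0. The totals reproduce.

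**2. Proportions and quotas.** Share = visits/6496; quota = 266 × share.

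| ASSIR | Stated share | Visits/6496 | 266 × stated | 266 × visits share | Stated quota |
|---|---|---|---|---|---|
| Mollet | 15.1% | 15.66% | 40.2 | 41.6 | 41 |
| Badalona | 29.6% | 29.76% | 78.7 | 79.2 | 79 |
| Granollers | 35.7% | 34.79% | 95.0 | 92.5 | 94 |
| Dreta Eixample | 19.6% | 19.80% | 52.1 | 52.7 | 52 |

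No stated share matches at one decimal. Mollet is 0.6 points low and Granollers 0.9 points high; the other two are 0.2 points low. By ordinary rounding, 41 and 94 follow from neither column. Rounding the visit-based figures down for the other three and giving Granollers the remainder would yield 266 − 41 − 79 − 52 = 94, but the protocol states no such rule. The largest gap from a visit-based quota is 94 − 92.5 = 1.5 women.

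**3. Arm sizes under each pairing.** The harmonic mean 2ab/(a + b) gives the equal-arm size with about the same precision.

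| Pairing | Arms | Harmonic mean |
|---|---|---|
| Mollet + Granollers v Badalona + Eixample | 135 v 131 | 133.0 |
| Mollet + Badalona v Granollers + Eixample | 120 v 146 | 131.7 |
| Mollet + Eixample v Badalona + Granollers | 93 v 173 | 121.0 |

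For the last row, 2 × 93 × 173/266 = 121, and 121/133 = 0.91, a loss of 9%.

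Correcting the shares does not cure this. The unrounded visit-based quotas give about 134/132, 121/145 and 94/172.

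**4. Power, ignoring clustering, after 15% loss.** Power = Φ[(0.20 − 1.96·SE₀)/SE₁], with SE₀ pooled and SE₁ unpooled.

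- 133 v 133 (113.05 each after loss): SE₀ = √(2 × 0.58 × 0.42/113.05) = 0.0656; SE₁ = √((0.2496 + 0.2176)/113.05) = 0.0643; z = 1.11; power 86.6%.
- 135 v 131: 86.6%.
- 120 v 146: 86.3-86.4%, depending on which arm is larger.
- 93 v 173 (79.05 and 147.05 after loss): 83.6% if the control arm is the smaller, 83.1% if the intervention arm is.

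This takes the 15% loss as contained in the 133. If it is not, the figures are 91.5% at 133 v 133 and 88.7-89.0% at 93 v 173.

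**5. Why these are not the trial's power.** The simple formula gives 95 per arm for 48% v 68% at 80% power, and 95/0.85 = 112 after loss. Reaching 133 implies a design effect of 133 × 0.85/95 = 1.19, and no ICC is given to check it. Taking the ICC as an assumption, and effective size as the sum over clusters of m/(1 + (m − 1)·ICC) with m after loss:

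| Assumed ICC | 135 v 131 | 93 v 173 |
|---|---|---|
| 0.001 | 84.6% | 81.8% |
| 0.01 | 67.9% | 66.5% |
| 0.05 | 33.9% | 33.9% |

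Moving down a column changes power far more than moving across a row. These figures use a normal approximation and do not allow for there being only two clusters per arm.

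**The case against.** The strongest reply is that little is lost. The 135/131 split misses the target by two women and has the same power as 133/133. The 120/146 split costs at most about 0.4 points. Only 93/173 has a visible effect, and even there the simple formula stays above the planned 80%. Once clustering enters, the relative cost of imbalance shrinks. All of this stands.

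It can also be said that considering hospital characteristics may already exclude 93/173. It may, but the protocol neither says how they will be used nor names the pairings allowed, so the bad split can be neither assumed away nor given a probability. A reader might count the allocations and infer a one-in-three chance of 93/173. The documents do not support that, because the restriction may make some pairings impossible.

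The proportion errors are clerical. They move no quota by more than about 1.5 women and do not cause the imbalance. That stands too, and it is why they are a secondary point.

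Finally, sampling in proportion to first visits is a deliberate choice. A remedy should keep it as far as possible rather than replace it with equal quotas.

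**Conclusion.** The contradiction holds and its effect is modest. Followed as written, Table 1 does not give 133 per arm under any pairing. It comes close in two of the three and misses clearly in the third, where effective size falls by 9% to 121 per arm. The power cost there is about 3 points (86.6% to 83.1-83.6%), assuming a two-sided 5% test, 15% loss contained in the 133, and no clustering.

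A reader might infer that the trial is therefore underpowered. The documents do not support that inference from the quotas: the loss is small, and actual power depends mainly on an ICC that is not stated and on having two clusters per arm.

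The Proportion column is wrong at one decimal in all four rows, materially for Mollet and Granollers. This is a correction to the table and not a threat to the design.

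**What to change.** Replace the single set of quotas by a rule: after allocation, each arm recruits 133 women, divided between its two ASSIRs in proportion to their first visits. For example, Mollet paired with Badalona gives 133 × 1017/2950 = 45.9, so 46 and 87. All cases:

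| Pairing | First arm | Second arm |
|---|---|---|
| Mollet + Badalona v Granollers + Eixample | 46 / 87 | 85 / 48 |
| Mollet + Granollers v Badalona + Eixample | 41 / 92 | 80 / 53 |
| Mollet + Eixample v Badalona + Granollers | 59 / 74 | 61 / 72 |

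Correct the Proportion column to 15.7, 29.8, 34.8 and 19.8% (the sum of 100.1 is rounding).

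The cost is one table and one sentence, with the total unchanged at 266. Allocation must in any case be known before recruitment, because only the intervention midwives attend the workshop. The largest quota for the smallest ASSIR is 59, against 1017 first visits a year. The small downside is that the sample no longer mirrors visit volume across arms, although it still does within each arm. Quotas of 66 and 67 in every arm would also give 133, but would abandon proportional sampling altogether.

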## Intervention

### Characteristics of the intervention in the control group.

Midwives in the prenatal control visit between 24 to 28 weeks of gestation will deliver the birth plan so that the pregnant woman can fill it out at her home. In the prenatal control visit between 29 to 33 weeks of gestation, the pregnant women will deliver the birth plan to the midwife and the pregnant women will be able to ask about the aspects they want. The midwives will then deliver the second birth plan to the pregnant women so that they can fill it out at home and then they must deliver a copy

to the midwife at the prenatal visit between 34 and 40 weeks of gestation.

The midwife will instruct the pregnant woman to present the original to the reference hospital.

#### Characteristics of the intervention in the intervention group

Phase I. Training intervention for midwives. There will be a 4-hour workshop on counselling in the birth plan, based on the communicative intervention of negotiation of options in shared decision making by Epstein et al, which consists of: understanding the experience and expectations of the pregnant woman, construction of a collaborative relationship between the pregnant woman and the professional, provide information according to the existing level of evidence and current recommendations, and verification of understanding and compliance 

Phase II. Intervention in pregnant women. The pregnant women will receive the birth plan from the midwives in the prenatal control visit between 24-28 weeks of gestation that they will complete at home. Later, in the prenatal control visit between 29-33 weeks of gestation, the pregnant women will receive the counselling intervention from the midwife, which will consist of standardized advice on the birth plan based on shared decision making according to Epstein et al  and in the delivery of an informative leaflet  based on the existing scientific evidence of the aspects expressed in the birth plan. The counselling of the midwife of the pregnant women will include the following activities: it will explore the previous experiences and expectations of the pregnant woman regarding the childbirth; establish with the pregnant woman a collaborative relationship in decision-making; explain the existing evidence for each aspect of the birth plan; will inform of the updated recommendations on the aspects specified in the birth plan and will check the understanding of the information provided to the pregnant woman. The midwife will then deliver a second birth plan that the pregnant woman will fill out at her home and that she must deliver a copy to the midwife at the prenatal visit between 34-40 weeks of gestation. The midwife will instruct the pregnant woman to present the original to the reference hospital.

